#### Secondary outcomes

Secondary outcomes will be collected across four areas:Implementation outcomesClinical endpointsClinical service delivery indicatorsWomen’s wellbeing and mental health

(1) Implementation outcomes

Using the RE-AIM framework [31], we will report the following implementation outcomes (Table 1):

**Table 1 Tab1:** Implementation outcomes to be assessed

RE-AIM dimension	Definition	Assessment measure	Data source	Timepoint
**Reach**	The number of people and percent of the target population who are impacted, and the extent to which those reached are representative and include those at most risk	Size of the target population	PHC records	Study end
		Number of women enrolled in the study and the number receiving the intervention	SHP app	Study end
		Comparison of characteristics of the individuals enrolled in the study to the target population	SHP app; district records	Study end
**Effectiveness**	A measure of the impact on health individual-level primary outcome including positive, negative and unintended consequences	The proportion of women with anaemia as measured by capillary test at 12 months after birth The proportion of women with follow-up blood pressure measurement or blood glucose tests during the 12 months after birth following a pregnancy affected hypertension or diabetes	Endline CRF	Study end
		The proportion of screening visits performed per protocol (maximum 7 SHP visits) The proportion of visits conducted in person and by phone The proportion of visits performed at the stated time in the protocol	Intervention group only: SHP app	Study end
		Self-report rating of health outcome (WHO-5 quality of life)	Endline CRF	Study end
		Self-report rating of health behaviour (WHO infant feeding questionnaire)	Endline CRF	Study end
		Quantitative comparison of outcomes across subgroups (family income, caste stratification, parity, rural/semi-rural, private/ government delivery) with qualitative exploration	Endline CRF, interviews and FGDs	Study end
**Adoption**	The number and percent of settings/providers/interventionists who participate, and the extent to which these are representative of those who the target population will use or visit	Number of PHCs invited and the number that participate at the start of the study	Baseline study information	Study initiation
		Number of participating PHCs at the end of the study	Endline study information	Study end

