*Implementation*: Fidelity to the intervention protocol for the trial and for the intervention itself and any adaptations during the trial. This will be measured assessing data completeness, and through qualitative methods with health workers.
*Maintenance*: We will explore the system-level factors needed for institutionalisation of the intervention and level of intent to continue to programme in the study settings and more widely using key stakeholder interviews and focus group discussions, as well as policy discourse analysis around maternal health and digital health policy.

(2)Clinical endpoints
*Anaemia*: Haemoglobin will be compared between intervention and EUC clusters as a continuous variable (measured in grams per decilitre on point-of-care test) and as categories of anaemia using the WHO thresholds used for non-pregnant adults: no anaemia > 12.0 g/dL; mild anaemia 11.0–11.9 g/dL; moderate anaemia 8.0–10.9 g/dL; severe anaemia < 8 g/dL
*Diabetes*: Between the intervention and EUC, we will compare venous blood glucose following a 2-h, 75-g oral glucose challenge at 1 year after birth in participants diagnosed with GDM during pregnancy. Blood glucose will be assessed as a continuous measure (in milligrams per decilitre) and as categories of glucose impairment: Normal: < 140 mg/dl, impaired glucose tolerance (IGT): 140–199mg/dl, Diabetes: ≥ 200 mg/dl
*Hypertension*: Blood pressure (BP) will be compared between women who developed HDP. BP will be assessed as a continuous measure (systolic, diastolic and mean arterial pressure) in millimetres of mercury (mmHg) using a validated sphygmomanometer and as a binary category of hypertension (yes/no) defined as BP > 140/90 mmHg(3)Clinical service delivery indicators
*Quality-of-care score*: We will measure differences between the intervention and EUC clusters using a quality-of-care score we have developed specifically for this study. The score comprises an equally weighted composite of clinical outcomes (anaemia, diabetes, hypertension) with measures of access and health professional visit frequency during pregnancy and in the first 12 months after delivery.

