*Follow-up after anaemia, GDM or HDP condition*: We will compare how many women with anaemia undergo a haemogloblin test; how many women after HDP or GDM undergo BP measurement, and how many women after GDM undergo a glucose assessment (fasting or random capillary glucose, OGTT or HbA1c) within 6 weeks and 6 months and 12 months after birth.(4)Women’s wellbeing, mental health, lactation practice
*Wellbeing*: The impact of the intervention on women’s general wellbeing, mental health. We will use locally validated mental health and wellbeing tools (EQ-5D-3L, PHQ9 and GAD7 [35]) to compare changes between baseline and at 12 months.
*Lactation*: is one of the few interventions for which evidence supports a positive impact on maternal and newborn long-term health following a high-risk pregnancy, specifically one affected by GDM [36]. We will assess whether the additional support provided through the intervention can improve lactation practice using WHO Infant and Young Child Feeding indicators [37].

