### Participant timeline {13}

PHCs will be recruited and randomised before individual participant recruitment commences. After randomisation, ASHAs in the intervention clusters will attend the education programme to receive training on the clinical conditions, use of the point-of-care devices and SMARThealth Pregnancy app. Individual participants will be approached by their ASHA worker to participate after 12 weeks’ gestation. If they consent to participate in the study, a study team member will complete a baseline assessment, which includes questionnaires, blood pressure and haemoglobin measurement. A study team member will perform a mid-point assessment between 9 and 12 weeks after birth to capture events and healthcare utilisation including out-of-pocket costs around the time of birth. A study team member will conduct the final study visit 9–12 months after delivery, which will involve completing questionnaires, and measuring haemoglobin and blood pressure (Table 2).

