### Methods for additional analyses (e.g. subgroup analyses) {20b}

Subgroup analyses will be performed for women with GDM and HDP separately and with both conditions. The analysis of secondary outcomes will be performed on all women reaching the study endpoint. A structured observation of health worker performance will be performed on a subsample of 200 women from 10 intervention and control PHC facilities to assess fidelity to the study intervention.

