## Discussion

This study will test the effectiveness and implementation of a community-based high-risk pregnancy screening and referral programme up to 1 year after birth. In rural India, as in many settings, women must attend antenatal appointments in a clinic or hospital to detect high-risk conditions. We hope to demonstrate that screening by community health workers in the woman’s village or home can be a practical approach to improving the detection of women with high-risk conditions, timely referral and evidence-based management. Uniquely, our intervention considers the impact of conditions detected during pregnancy on women’s longer-term health, with repeated assessments during the first year after birth. We hope to demonstrate that this is a practical approach to implement effective interventions for reducing the endemic problem of anaemia amongst women in India and engaging women who develop GDM or HDP with postnatal screening for diabetes and hypertension. In particular, the mixed quantitative and qualitative data collection in this hybrid effectiveness implementation study will help us analyse implementation outcomes and identify implementation strategies which are context-sensitive and can address implementation barriers of the programme.

The SMARThealth Pregnancy intervention aims to support government efforts to reduce anaemia rates through improved understanding by ASHAs and capacity to perform point-of-care haemoglobin testing. This is in keeping with AMB recommendations.

Our study has several strengths. The pragmatic nature of the trial will generate evidence of the effectiveness of strategies to improve the care of women at high risk of postnatal anaemia, type 2 diabetes or hypertension. Community follow-up after a pregnancy affected by these conditions is not routinely performed in rural India, which misses critical opportunities for prevention.

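### Secondary glucose, blood-pressure and follow-up comparisons are made within GDM, HDP or anaemia groups whose membership the intervention can change, so randomisation does not protect them

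*Protocol article*

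**What the plan says.** The analysis groups are written into the outcome definitions (Protocol article, Outcomes {12}, Secondary outcomes):

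- Glucose is compared "at 1 year after birth in participants diagnosed with GDM during pregnancy".
- For hypertension, "Blood pressure (BP) will be compared between women who developed HDP".
- Follow-up testing covers three condition-defined groups: "We will compare how many women with anaemia undergo a haemogloblin test"; "how many women after HDP or GDM undergo BP measurement"; and glucose assessment is counted among women who had GDM. Table 1 has a related RE-AIM measure, testing "during the 12 months after birth following a pregnancy affected hypertension or diabetes".

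Methods for additional analyses {20b} adds: "Subgroup analyses will be performed for women with GDM and HDP separately and with both conditions". The next sentence there puts secondary outcomes on every woman who reaches the end of the study, without saying how this fits the narrower groups above.

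Participant timeline {13} has PHCs randomised, and intervention ASHAs trained, before women are recruited. Intervention description {11a} gives intervention ASHAs point-of-care tests, app reminders and decision support that covers blood pressure and GDM screening. The section on the SMARThealth programme names better identification and diagnosis as the purpose, and the Discussion hopes to show "a practical approach to improving the detection of women with high-risk conditions".

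**The concern.** A comparison between arms is protected by randomisation when the women compared are defined before allocation, or by something allocation cannot alter. A GDM or HDP label meets neither condition here. It is acquired largely after the PHC has been allocated, and one arm receives a package intended to make the label more common among women who have the condition. The labelled women in the two arms may then differ in severity or other features before any treatment effect.

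Two things are at stake. Glucose and blood pressure among labelled women could differ between arms with no true effect, or a true effect could be masked. Follow-up percentages could also mislead, because a woman whose condition is never found drops out of the denominator and the missed care goes uncounted. Screening and follow-up after these conditions is a named part of Objectives {7}. The discussion of bias in the article covers recruitment, blinding and benefit in control clusters, but not this.

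**Working it through.** The document has no figure on this point to reproduce. It gives no detection rate or severity mix by arm. The only calculated figure is the sample size for the primary outcome, which the point does not touch. The check is therefore a reading of the text plus illustrations. **All inputs to the illustrations are assumed unless a source is given.**

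**1. Is the grouping settled after randomisation and open to the intervention?** Randomisation of PHCs comes first (Participant timeline {13}). The extra antenatal testing and prompting is described only for the intervention arm (Intervention description {11a}). The study team's own visits, the same in both arms, are one baseline visit in pregnancy and two after birth (Plans for assessment and collection of outcomes {18a}). One antenatal blood-pressure reading, possibly as early as 12 weeks, cannot find HDP equally in both arms, and the baseline visit as described lists no glucose test. So yes, for GDM and HDP. For anaemia the study team does measure baseline haemoglobin in both arms, but the follow-up outcome does not say that this defines the group.

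**2. Spurious difference when severe cases are found first.** Assume no true effect. Half of true cases are marked (30% abnormal at 1 year) and half mild (10%), and all marked cases are found before any mild one. For a detected share d of at least 0.5:

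p(d) = [0.5 × 0.30 + (d − 0.5) × 0.10] / d

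| Detection, control vs intervention | Control | Intervention | Difference |
|---|---|---|---|
| 50% vs 90% | 0.15/0.5 = 30.0% | 0.19/0.9 = 21.1% | −8.9 points |
| 60% vs 80% | 0.16/0.6 = 26.7% | 0.18/0.8 = 22.5% | −4.2 points |
| 70% vs 90% | 0.17/0.7 = 24.3% | 0.19/0.9 = 21.1% | −3.2 points |

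If detection is unrelated to severity, each arm shows 0.5 × 0.30 + 0.5 × 0.10 = 20% at any detection rate, and the difference is 0. Reversing the order of detection reverses the sign.

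**3. A second set of assumptions.** Assume no true effect; half of cases marked (40%) and half mild (15%); 90% of marked cases found in both arms; 90% of mild cases found in the intervention arm and a share s in control.

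p = (0.9 × 0.40 + s × 0.15) / (0.9 + s)

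- Intervention: 0.495/1.8 = 27.5%.
- Control, s = 0.4: 0.42/1.3 = 32.3%, difference −4.8 points.
- Control, s = 0.6: 0.45/1.5 = 30.0%, difference −2.5 points.
- Control, s = 0.8: 0.48/1.7 = 28.2%, difference −0.7 points.
- Control, s = 0.9: 27.5%, difference 0.

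For scale, the plan implies 108 × 15 × 0.8 = 1,296 completers per arm. With an assumed true GDM prevalence of 10% there are about 130 cases per arm. The diagnosed control groups would then be about 84, 97, 110 and 117 women, against 117 in the intervention arm. Among all women the true difference is zero in every row.

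**4. Follow-up percentages.** Assume 100 true cases per arm. Control diagnoses 50 and tests 25; intervention diagnoses 90 and tests 45. The planned measure reads 25/50 = 50% against 45/90 = 50%. Over all true cases it is 25% against 45%. Here the chosen denominator hides a gain.

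**The case against.** The best reply has five parts.

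- **Both arms share some ascertainment.** Training on the glucose tolerance test goes to all PHCs (section {6b}), GDM is called at one fixed threshold, HDP is defined by a published guideline (Abbreviations), and the study team takes blood pressure at baseline in both arms. This stands as mitigation. It equalises the criterion and some of the skill, but not how often women are tested or prompted.
- **Direction.** A reader might infer that extra mild cases in the intervention arm will make it look protective. The document does not support that as fact. Missed GDM may mean an untested woman and not a milder one. The sign is unknown, and zero belongs in the range.
- **Timing.** A reader might also infer that every diagnosis follows enrolment. Eligibility for women allows enrolment at any time from 12 weeks, so a late enrolee may already be diagnosed. What reliably comes before recruitment is allocation of the PHC and training of its ASHAs.
- **The objective is itself conditional.** It speaks of follow-up after an affected pregnancy, so a percentage among affected women is a natural thing to report. This stands: that percentage should be kept, with others beside it.
- **The analysis plan can settle it, and section {20b} already uses all women.** The article promises a detailed plan, but the groups are fixed in the outcome definitions, which a plan would inherit. The sentence in {20b} reads most easily as describing completers and does not clearly lift the restriction.

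**Conclusion.** The point holds for the secondary outcomes. Comparisons of glucose, blood pressure and follow-up testing within GDM or HDP groups, and the subgroup analyses in {20b}, condition on a status that the intervention is designed to change. Anaemia follow-up shares the weakness unless its group is tied to the baseline measurement.

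The size cannot be derived from the document. Under the assumed inputs with no true effect, the spurious difference in 1-year abnormality runs from 0 to about 9 percentage points. The upper end needs strict severity-ordered detection and a 50% against 90% gap. Follow-up percentages can be distorted as well.

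A reader might go further and conclude that the trial's evidence on diabetes and hypertension is invalid. That is not supported. The primary outcome, its sample size and the stated significance criterion are not restricted to diagnosed women. The quality-of-care score is compared between clusters with no stated restriction of this kind. Endline blood pressure is planned for everyone. This should be fixed, but it does not threaten the main result.

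**What to change.** 1. **Hypertension.** Make the between-arm comparison of endline blood pressure and hypertension in all women with a final visit the main analysis. The final visit is one "which will involve completing questionnaires, and measuring haemoglobin and blood pressure", so no new data are needed.
2. **Anaemia follow-up.** Define the denominator by the study team's baseline haemoglobin, measured in both arms.
3. **GDM and HDP follow-up.** Report by arm the share diagnosed, and the share diagnosed and then tested among all enrolled women, alongside the percentages among affected women.
4. **GDM-only and HDP-only contrasts**, including 1-year glucose and the {20b} subgroups: label them descriptive and not randomised. Glucose is not among the measurements named for all women at the final visit, so no all-women version is available from the visits as described.
5. **Reconcile** the all-women sentence in {20b} with the restricted groups in the outcome definitions.

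The cost is wording and a few tables, and the article promises its detailed analysis plan before unblinding. There are real downsides. All-women contrasts dilute any effect confined to high-risk women. The all-enrolled follow-up measure merges detection with follow-up and can rise through diagnosis alone. Baseline haemoglobin misses anaemia that arises later in pregnancy.

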### Participant timeline {13}

PHCs will be recruited and randomised before individual participant recruitment commences. After randomisation, ASHAs in the intervention clusters will attend the education programme to receive training on the clinical conditions, use of the point-of-care devices and SMARThealth Pregnancy app. Individual participants will be approached by their ASHA worker to participate after 12 weeks’ gestation. If they consent to participate in the study, a study team member will complete a baseline assessment, which includes questionnaires, blood pressure and haemoglobin measurement. A study team member will perform a mid-point assessment between 9 and 12 weeks after birth to capture events and healthcare utilisation including out-of-pocket costs around the time of birth. A study team member will conduct the final study visit 9–12 months after delivery, which will involve completing questionnaires, and measuring haemoglobin and blood pressure (Table 2).

**Table 2 Tab2:**
[figure not shown]
Participant timeline of assessments

PP = post partum. T_1_ = 12 weeks pregnancy; T_2_ = Third trimester; T_3_ = week one post birth; T_4_ = week 6 post birth; T_5_ = week 10 post birth; T_6_ = week 14 post birth; T_7_ = months 9-12 post birth. Visit intervals timed to be in line with Indian infant immunisation schedule

### Sample size {14}

The sample size was calculated using anaemia as the primary outcome. Three aspects were considered in determining the sample size:

Intracluster correlationCluster size and numberVariability in the primary outcome and estimated reduction that could be achieved by the intervention

These risks were balanced with operational considerations

#### Intracluster correlation

The nature of the intervention as a health system intervention precludes individual randomisation. Estimating intracluster correlation coefficients (ICCs) was based on the SMARThealth Pregnancy pilot study extrapolations [38]. Across the four sites in the pilot study, the ICC for anaemia was 0.019; thus, an ICC of 0.02 has been assumed for the study.

#### Cluster size and number

Clusters (i.e. PHCs) of various population sizes and birth numbers will be enrolled in the study. For operational reasons, a maximum cluster number of 30 is proposed, with two villages per cluster selected. Each village has one affiliated ASHA; thus, a minimum of 120 ASHAs will be needed.

#### Variability in the primary outcome and estimated effect size

The pilot study’s prevalence of anaemia during pregnancy was higher than the reported national levels, likely due to selection differences and differences in testing techniques (venous sample vs POC device used in the pilot study).

The prevalence of anaemia is slightly higher in non-pregnant than pregnant women (national estimate for India 53 and 50% respectively, NFHS 5 [39]). The national target for anaemia reduction is three percentage points per year as part of the Anaemia Mukt Bharat programme [18].

We estimate that our intervention will improve anaemia rates in these populations by 9% over 3 years (i.e. 53 to 44%). Determining a minimally clinically important threshold for anaemia is challenging. We selected the target decrease in anaemia as it was in keeping with the AMB programme [18], and to be an achievable and programmatically meaningful target with optimal support for anaemia prevention. Whilst anaemia is anticipated to decrease in the population because of the ongoing government programmes (including AMB), evidence from our pilot study is that compliance and implementation issues exist on the ground. Our intervention was designed to enhance delivery of the government programme and reaching of national anaemia reduction targets.

Given 30 clusters and an ICC of 0.02, 86 women per cluster are needed to detect a 9% absolute reduction (53 to 44%) with 80% power (a total sample size of 2580). Allowing for losses to follow-up of 20%, a sample size of 108 women per cluster is needed (a total sample size of 3240).

### Recruitment {15}

Each district will produce a list of all PHCs, with population size, number of ASHAs and number of births in the previous 12 months. After obtaining relevant permissions from the District Medical and Health Officer, the head of each PHC deemed eligible will be approached. Once they have consented to participate, the PHC will be randomised to either intervention or enhanced usual care.

Individual women will be identified by ASHAs affiliated with each PHC and by review of PHC records for women registered in the area for antenatal care. Women will be approached by the ASHA and given information about the study, then asked whether they agree to participate.

## Assignment of interventions: allocation

### Sequence generation {16a}

Before randomisation, each PHC will be paired with another similar PHC from the same state and with similar characteristics. The pairing will be based on:

State (Telangana or Haryana)Distance in km to the district headquartersPHC total population sizeLocal advice on population similarity (socio-economic, demographic, etc.).

Within each PHC pair, one PHC will be randomly allocated to intervention using a computer-generated randomisation programme. The other PHC will then be designated as the control. To ensure a 1:1 balance (the same number of PHCs allocated to intervention and to control) within each state, we will select an even number of PHCs in each state. Sixteen PHCs will be enrolled from Telangana and 14 from Haryana.

